	**Every 12 weeks ± 14 days after last treatment administration**	
Survival status	X	X
Diagnosis of new malignancy	X	X
Subsequent anti-cancer therapy	X	X
Pregnancy test for WOCBP	Pregnancy test is to be renewed/repeated for 6 months after last protocol treatment	
Health-related quality of life (HRQoL)	X	X
Disease evaluation (cMRI)	X	

*WOCBP* Women of childbearing potential, *HRQoL* Health-related quality of life, *cMRI* Contrast magnetic resonance imaging

### Statistical considerations and data management

A total sample size of 411 patients is needed to detect an increase from an expected median OS of 9 months [17, 18] in the control arm to 12.5 months in the experimental arm based on a one-sided log-rank test at a significance level of 2.5% and a power of 80%, corresponding to a hazard ratio of 0.72. An increase of 3.5 months of survival when radiotherapy is added to lomustine would be considered clinically significant. Stratification factors will include country, *MGMT* promoter methylation status (unmethylated vs methylated vs unknown), steroid use at study entry (no, yes), and WHO performance status (0, > 0). There will be an interim futility and efficacy analysis organized after observation of 97 OS events (33%). The primary analysis will be performed in the intent-to-treat population (ITT), i.e., all randomized patients according to the arm they were allocated to. In the per protocol population, all randomized patients who have started their allocated treatment (i.e., at least one dose of lomustine or lomustine and radiotherapy) will be analyzed. In the per protocol population, patients will be classified and analyzed in the arm they were assigned at the time of enrolment. For data management procedures, EORTC, in its role of sponsor and data controller of the clinical study ensures that the processing activities on the personal data in scope of this study are compliant with, but not limited to, the requirements set by EU General Data Protection Regulation (GDPR EU 2016/679), its subsequent amendments and any additional national laws, recommendations, and guidelines as applicable. All data are collected via an electronic case report form by study staff with confirmed GCP certification named on delegation logs at the trial sites and are stored in secure database at EORTC Headquarter. The name of patients enrolled in the trial will neither be asked for nor recorded at the EORTC headquarters. A sequential identification number will be automatically allocated to each patient registered in the trial. This number will identify the patient and will be included on all case report forms and corresponding material and data associated with the patient. In order to avoid identification errors, the patient’s code (maximum of four alpha numerics) and year of birth will also be reported on the case report forms. Data collected during the course of the research will be kept strictly confidential and only accessed by members of the trial team (or individuals from the Sponsor organization or center sites where relevant to the trial). The EORTC headquarters will perform on-site and/or remote monitoring visits according to the approved study monitoring plan in order to maximize protocol adherence, correct false data entries, and minimize missing data. No imputation will be used to account for missing data. The first visit in a participating site will be performed within 6 to 12 months after the first patient’s enrolment at this site. Frequency and number of subsequent visits will depend on site’s accrual and quality observed during the previous visit. Reporting of adverse events indicating expectedness, seriousness, severity, and causality will be performed according to ICH GCP and EU Regulation 536/2014. At the trial sites, all reporting of adverse events must be done by the principal investigator or authorized staff member and will be transmitted electronically to the pharmacovigilance department of EORTC. As the sponsor, EORTC will be responsible for the reporting of suspected unexpected serious adverse reaction (SUSARs)/unexpected serious adverse reaction (SARs) to the competent authorities, ethics committees, EudraVigilance Clinical Trial Module (EVCTM), and all participating investigators as applicable. Medical review will be performed on a regular basis by a medical representative at EORTC and with the support of the principal investigator. Data collected during the course of the research will be kept strictly confidential and only accessed by members of the trial team (or individuals from the sponsor organization or center sites where relevant to the trial). The independent data monitoring committee for EORTC studies (IDMC) is in charge of the independent oversight of this study, according to the EORTC policies. LEGATO is an open-label trial and trial participants, care providers, outcome assessors, and data analysts will not be blinded. The clinical trial is registered at ClinicalTrials.gov with the identification number NCT05904119.

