OS is defined as the number of days from the date of enrolment to the date of death due to any cause. If a subject has not died, the data will be censored at the last date documented to be alive. PFS will be defined as the number of days from the date of enrolment to the date of earliest radiological disease progression or to the date of death due to any cause, if disease progression did not occur. Patients for whom neither death nor progression have been documented will be censored at the date of the last radiological assessment that the patient was progression-free.

Radiological follow-up for the evaluation of PFS and response rate will be performed by cranial MRI every 12 weeks. MRI will be assessed according to Response Assessment in Neuro Oncology (RANO) criteria interpretation by the local investigator.

Toxicity reporting will be done according to the Common Terminology Criteria for Adverse Events (CTCAE) version 5.0. Neurocognitive functioning will be assessed using Mini-Mental State Examination (MMSE) every 6 weeks and the NANO scale will be utilized for evaluation of neurological function. Health-related Quality of Life (HRQoL) will be assessed every 6 weeks using EORTC Quality of Life Questionnaire (QLQ)-C30, QLQ-BN20 Brain tumor module and one additional item from the EORTC Item Library (IL)-46.

Self-reported HRQoL data will be transformed into health utility values for subsequent health economic analyses. To this end, the EORTC QLQ-C30 data collected for each study subject and at each HRQoL assessment time point will be mapped to health utility values using an established indirect mapping approach [15, 16]. In the adopted indirect mapping approach, first the probabilities of belonging to European Quality-of-Life-5 Dimensions (EQ-5D) categories will be calculated, and then the corresponding EQ-5D scores will be translated into health utility values using a country-specific value set for the conversion [16].

Tables 4, 5, and 6 summarize study calendar before treatment start, during treatment, and during follow-up. Data will be captured in electronic case report forms.

**Table 4 Tab4:** Study calendar—before treatment started

Assessment	Within 14 days prior to enrolment	Within 7 days prior to enrolment
Disease evaluation (cMRI)	X	
Complete medical history	X	
Concomitant medication		X
Vital signs		X
ECOG/WHO performance status		X
Clinical examination		X
Pulmonary function test		X
Mini-Mental State Examination (MMSE)		X
NANO scale		X

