#### Control arm: lomustine

In the control arm, lomustine will be given at a recommended dose of 110 mg/m^2^ (maximum absolute dose 200 mg, minimum dose 80 mg) every 6 weeks. The maximum cumulative dose must not exceed 1000 mg/m^2^ to prevent pulmonary toxicity [19]. Participants must start lomustine within 7 days of enrolment. Treatment will be administered until disease progression, unacceptable toxicity, death, or until the occurrence of any predefined withdrawal criterion such as withdrawal of patient consent or safety concerns. Lomustine has a well-known safety profile that includes fatigue, hematological symptoms, and on rare occasions, the development of pulmonary toxicity after more than 6 months of treatment and a cumulative dose of 1000 mg/m^2^. Hematological toxicity, as the main concern in the treatment by lomustine occurs usually after 4 weeks after drug administration. Recommendations for dose modifications follow published guidelines [20].

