#### Experimental arm: lomustine plus reirradiation

In the experimental arm, radiotherapy with a prescribed dose of 35 Gy (daily dose 3.5 Gy, 10 fractions) over 2 weeks will be delivered in addition to the same chemotherapy regimen as in the control arm (lomustine 110 mg/m^2^ every 6 weeks). Lomustine should be started within 7 days of enrolment. Radiotherapy should start within 14 days of randomization and/or within 7 days of the first lomustine intake. Megavoltage equipment able to deliver stereotactic, intensity-modulated radiotherapy (IMRT) or volumetric modulated arc therapy (VMAT) is required.

Radiotherapy delineation will be performed on a magnetic resonance (MR) image with contrast agent administration. Treatment planning using volumetric modulated arc therapy (VMAT) and image-guided radiation therapy (IGRT) is advised. IMRT or VMAT planning is allowed. Intensity-modulated radiation therapy (IMRT) and three-dimensional conformal radiotherapy are allowed.

The maximum diameter of contrast enhanced recurrent tumor allowed for inclusion in the trial is 5 cm. In case of multifocal disease, the lesions must be in proximity to one another, to be treated with a single isocenter, and the maximum cumulative tumor diameter is 5 cm.

The gross tumor volume (GTV) will be defined using the MRI images as a T1-weighted contrast enhancing lesion (contrast-enhanced CT for patients who cannot undergo MRI). In patients who undergo surgery, the GTV is defined by the post-operative resection cavity plus any residual enhancing tumor.

A clinical tumor volume (CTV) expansion of maximum 5 mm can be applied at the investigator discretion for lesions measuring less than 4 cm in maximum diameter or for new lesions. CTV is cropped out around natural fixed barriers for tumor spread (skull, falx, tentorium). Otherwise, no additional CTV expansion will be added.

An appropriate planning target volume (PTV) expansion, justified based on image guidance and immobilization, will be applied. Regardless, the PTV expansion should be no smaller than 2 mm. Daily image-guided radiation therapy (IGRT) is required for institutions utilizing PTV margins of less than 5 mm.

Normal tissue limits will be defined according to the ESTRO-EORTC consensus on reirradiation, reflecting possible overlap with previous radiation target or critical organs at risk with concern of toxicity from cumulative doses [21].

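### The per-protocol entry rule appears to ask for more in the experimental arm than in control, so patients lost between lomustine and radiotherapy leave one arm only

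*Protocol article*

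**What the plan says.** All references are to the protocol article.

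- *Statistical considerations and data management* makes intention-to-treat primary: "The primary analysis will be performed in the intent-to-treat population (ITT), i.e., all randomized patients according to the arm they were allocated to".
- The same section defines the per-protocol population as randomised patients who "started their allocated treatment (i.e., at least one dose of lomustine or lomustine and radiotherapy) will be analyzed", and adds: "In the per protocol population, patients will be classified and analyzed in the arm they were assigned at the time of enrolment". A patient who does not qualify is therefore left out, not moved to the other arm.
- *Interventions* names the two allocated treatments as lomustine alone and lomustine plus radiotherapy.
- Lomustine has the same start window in both arms: "Participants must start lomustine within 7 days of enrolment" (*Control arm: lomustine*) and "Lomustine should be started within 7 days of enrolment" (*Experimental arm: lomustine plus reirradiation*).
- Radiotherapy has its own window: "Radiotherapy should start within 14 days of randomization and/or within 7 days of the first lomustine intake".
- *Objectives and endpoints* sets the time origin: "OS is defined as the number of days from the date of enrolment to the date of death due to any cause".

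**The concern.** The bracket in the per-protocol definition lists two conditions, and they match the two allocated treatments. On that reading, control patients qualify at the first lomustine dose, and experimental patients qualify only once radiotherapy has also begun, usually some days later.

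Take two identical patients who swallow lomustine on day 3 and die or become unfit on day 8, before any radiotherapy. The control patient's early death counts. The experimental patient's does not. With time counted from enrolment, patients kept in the experimental arm cannot have died before radiotherapy began, and no matching condition applies to control after the first dose. The trial is also open-label, so the decision not to start radiotherapy is taken knowing the arm.

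At stake is how far a per-protocol survival result can be trusted as support for the primary result. Its error would run in one direction, in favour of radiotherapy.

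**Working it through.** **Planning figures.** The design assumes an "increase from an expected median OS of 9 months [17, 18] in the control arm to 12.5 months in the experimental arm". The ratio is 9/12.5 = 0.72, as stated. Events needed (Schoenfeld, one-sided 2.5%, 80% power): 4 × (1.960 + 0.842)² / (ln 0.72)² = 291. The interim at 97 events is 97/291 = 33.3%, which agrees with the stated 33%. These figures belong to the intention-to-treat test and are not in question. The article gives no per-protocol figures to reproduce.

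**Early deaths at the planning medians** (assumption: exponential survival; 9 months = 273.9 days, 12.5 months = 380.5 days). P(death by day d) = 1 − 2^(−d/median).

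- Median 9 months: 1.8% by day 7, 3.5% by day 14.
- Median 12.5 months: 1.3% by day 7, 2.5% by day 14.

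**Deaths in the one-sided gap.** Assume lomustine starts uniformly on days 0–7 and radiotherapy 0–7 days after it, a mean gap of 3.5 days.

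- No effect: 0.693/273.9 × 3.5 = 0.9%, or about 1.8 of 205 patients.
- Design effect: 0.693/380.5 × 3.5 = 0.6%, or about 1.3 of 205 patients.

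Rough effect on the hazard ratio: if about 294/411 = 71.5% of patients have died at the analysis, removing 0.9% of the arm as deaths removes 0.9/71.5 = 1.3% of its events, with almost no loss of follow-up time. So 1.00 becomes about 0.99. With 0.6%, the loss is 0.9% and 0.72 becomes about 0.71. Simulation (33 months of uniform accrual, taken from the recruitment dates) gives the same values.

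**If more patients miss radiotherapy.** The article gives no non-start rate, so a range is assumed. In addition to the gap deaths, a share of the experimental arm never starts radiotherapy and dies within two months. To judge plausibility, compare that share with all such deaths still in the arm, here with radiotherapy starting uniformly on days 1–14.

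- No effect: 1 − 2^(−2/9) = 14.3% die within two months. About 2.0% are already excluded before treatment is complete, leaving 12.3%.
- Design effect: 1 − 2^(−2/12.5) = 10.5%, less about 1.4%, leaving 9.1%.

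| Extra non-starters who die within 2 months (assumed) | HR if truth is 1.00 | HR if truth is 0.72 | Share of remaining 2-month deaths this needs (no effect / design effect) |
|---|---|---|---|
| none | 0.99 | 0.71 | – |
| 1% | 0.98 | 0.70 | 8% / 11% |
| 3% | 0.95 | 0.68 | 24% / 33% |
| 5% | 0.93 | 0.66 | 41% / 55% |
| 8% | about 0.90 | about 0.63 | 65% / 88–89% |

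The 8% row asks that most early deaths occur in patients who never began radiotherapy, although it is due within about two weeks.

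**Check on a common rule.** With entry at first lomustine dose in both arms, the simulation returns 1.00 and 0.72. The tilt comes from the arm-specific condition.

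**The case against.** Several points on the other side are sound.

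- **The wording is not conclusive.** The sentence does not tie each condition to an arm, and does not say whether lomustine without radiotherapy counts as started. If one lomustine dose were enough in both arms, there would be no asymmetry. But the second half of the bracket would then add nothing, so the sentence needs correcting on either reading.
- **There may be no gap.** The radiotherapy window is written with an and/or, so radiotherapy could start with or before lomustine. For such patients the one-sided interval disappears.
- **The population is selected for fitness.** Performance status 0–2, steroids stable or falling, and recovery from any surgery make very early deaths less likely than the exponential model implies.
- **Not every missed start biases the result.** Patients of ordinary prognosis who refuse or meet planning delays can be excluded without shifting the hazard ratio in this way.
- **Conditioning on treatment received is what per-protocol sets do.** That is true, and in an add-on trial the conditions naturally differ. It does not remove the bias when survival is counted from before the condition is met.

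A reader might infer more than the documents support: that all early failures are removed from the experimental arm only, that the primary result is compromised, or that a planned confirmatory survival analysis is materially wrong. Failures before any lomustine leave both arms. The primary analysis keeps everyone randomised. The article assigns no endpoint or test to the per-protocol set, so its use for overall survival is an inference. Hazard ratios near 0.90 or 0.63 need a non-start rate that the article does not give.

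**Conclusion.** The point holds on the natural reading of the definition: the entry condition is stricter in the experimental arm, and failures between first lomustine and radiotherapy are excluded from that arm alone. Any per-protocol comparison of overall survival from enrolment would favour radiotherapy.

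The size that follows from the planned windows is small: about one to two extra exclusions among some 205 patients. Larger shifts are conditional on poor-prognosis patients often failing to start radiotherapy. All sizes assume exponential survival at the planning medians and the start-time patterns stated above.

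The direction is more certain than the size. The primary inference, the 411 patients and the event target stand. This is a minor point, confined to a supportive analysis.

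**What to change.** Rewrite the definition so that both arms enter by the same event: randomised patients with at least one lomustine dose, analysed as randomised.

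If a set requiring radiotherapy start is kept, fix one landmark day after the radiotherapy window. Apply the same condition (alive and still on protocol) to both arms, and count survival from that day. This removes the early-death part of the bias. Some selection on fitness may remain, so report exclusions by arm with reasons.

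The cost is a sentence or two, with no extra data or patients. The lomustine-based set keeps a few experimental patients who had no radiotherapy. A landmark drops early deaths in both arms: at day 14, for illustration, about 3.5% × 205 = 7 in control and 2.5% × 205 = 5 in the experimental arm at the planning medians. The choice should be fixed before survival data by arm are seen, because the article states that analysts are not blinded.

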
### Interventions

Patients will be randomized by EORTC in a 1:1 ratio to the control arm of lomustine alone or the experimental arm of lomustine plus radiotherapy.

#### Control arm: lomustine

In the control arm, lomustine will be given at a recommended dose of 110 mg/m^2^ (maximum absolute dose 200 mg, minimum dose 80 mg) every 6 weeks. The maximum cumulative dose must not exceed 1000 mg/m^2^ to prevent pulmonary toxicity [19]. Participants must start lomustine within 7 days of enrolment. Treatment will be administered until disease progression, unacceptable toxicity, death, or until the occurrence of any predefined withdrawal criterion such as withdrawal of patient consent or safety concerns. Lomustine has a well-known safety profile that includes fatigue, hematological symptoms, and on rare occasions, the development of pulmonary toxicity after more than 6 months of treatment and a cumulative dose of 1000 mg/m^2^. Hematological toxicity, as the main concern in the treatment by lomustine occurs usually after 4 weeks after drug administration. Recommendations for dose modifications follow published guidelines [20].

#### Experimental arm: lomustine plus reirradiation

In the experimental arm, radiotherapy with a prescribed dose of 35 Gy (daily dose 3.5 Gy, 10 fractions) over 2 weeks will be delivered in addition to the same chemotherapy regimen as in the control arm (lomustine 110 mg/m^2^ every 6 weeks). Lomustine should be started within 7 days of enrolment. Radiotherapy should start within 14 days of randomization and/or within 7 days of the first lomustine intake. Megavoltage equipment able to deliver stereotactic, intensity-modulated radiotherapy (IMRT) or volumetric modulated arc therapy (VMAT) is required.

Radiotherapy delineation will be performed on a magnetic resonance (MR) image with contrast agent administration. Treatment planning using volumetric modulated arc therapy (VMAT) and image-guided radiation therapy (IGRT) is advised. IMRT or VMAT planning is allowed. Intensity-modulated radiation therapy (IMRT) and three-dimensional conformal radiotherapy are allowed.

The maximum diameter of contrast enhanced recurrent tumor allowed for inclusion in the trial is 5 cm. In case of multifocal disease, the lesions must be in proximity to one another, to be treated with a single isocenter, and the maximum cumulative tumor diameter is 5 cm.

The gross tumor volume (GTV) will be defined using the MRI images as a T1-weighted contrast enhancing lesion (contrast-enhanced CT for patients who cannot undergo MRI). In patients who undergo surgery, the GTV is defined by the post-operative resection cavity plus any residual enhancing tumor.

A clinical tumor volume (CTV) expansion of maximum 5 mm can be applied at the investigator discretion for lesions measuring less than 4 cm in maximum diameter or for new lesions. CTV is cropped out around natural fixed barriers for tumor spread (skull, falx, tentorium). Otherwise, no additional CTV expansion will be added.

An appropriate planning target volume (PTV) expansion, justified based on image guidance and immobilization, will be applied. Regardless, the PTV expansion should be no smaller than 2 mm. Daily image-guided radiation therapy (IGRT) is required for institutions utilizing PTV margins of less than 5 mm.

Normal tissue limits will be defined according to the ESTRO-EORTC consensus on reirradiation, reflecting possible overlap with previous radiation target or critical organs at risk with concern of toxicity from cumulative doses [21].

The main toxicity expected from re-irradiation is radionecrosis in less than 10% of cases. The increased, synergistic, risk of hematological toxicity in the combination of lomustine and reirradiation is expected to be minimal.

### Study intervention compliance

A record of the number of tablets dispensed to and taken by each patient will be maintained and reconciled with study intervention and compliance records. Intervention start and stop dates, including dates for intervention delays and/or dose reductions will also be recorded in the electronic case report forms.

### Supportive care and concomitant medications

Supportive care is left at the investigator’s discretion, but adherence to the EANO recommendations is advised [20].

Prohibited medications include live or attenuated vaccines at any time during the study and for a period of 3 months after treatment discontinuation. Yellow fever vaccine is strictly contraindicated because of the risk of fatal systemic vaccinal disease. Patients must not receive salicylates due to increased risk of bleeding in case of thrombocytopenia. Any concomitant systemic therapy intended for the treatment of cancer, whether health authority-approved or experimental, is prohibited.

Permitted medications considered necessary for a participant’s welfare according to the local investigator include growth factors in accordance with ASCO guidelines for secondary prophylaxis and steroids as anti-emetics or part of symptom management [22].

SPIRIT reporting guidelines for publication of clinical trials protocols [23] were used and were submitted as an additional file (see Additional file 1).

